### The AIRE study design

The design of the AIRE operational research study will incorporate data from several cross-sectional studies and one prospective interventional cohort study with short-term 14-day follow-up for the severe cases. The recruitment and collection of mixed quantitative and qualitative data will be carried out over a period of 22 months from March 2021 to November 2022 in the four countries. The collection of individual IMCI data on children carried out over a period of 12 months (June 2021 to June 2022) will allow to consider any effect of seasonality for pneumonia, malaria and malnutrition.

#### Context evaluation

First, an exhaustive cross-sectional baseline survey of infrastructures, health personnel and site organization conducted in all PHC and referral hospitals where the AIRE project will be implemented (AIRE site assessment) was carried out before the introduction of the PO between March and July 2020. The objective was to map the project sites, to guide the selection of research sites and to assess the needs for upgrading the centers.

Secondarily, a prospective description of monthly PHC-level indicators will be provided for all AIRE sites after the introduction of the PO using aggregated data over the entire period of children’s enrollment: infrastructure, equipment (PO and oxygen availability), staff changes, and all IMCI consultation features.

#### Process evaluation

The AIRE project is a complex intervention, which involves a large number of actors, aims to implement plenty of activities and can be influenced by many elements external to the project (national policies, other Non-Governmental Organization (NGO)’ interventions, socio-economic context, etc.). To deal with this complexity, process evaluation will use mixed methods and will be based on a theoretical approach to evaluation [38] and more particularly on a realist approach to evaluation [39]. This approach aims to understand why an intervention works (or not), how, for whom and in which contexts.

A realistic evaluation relies on the principles of scientific realism [40]. It is based on the idea that an intervention does not work by itself and is not what produces an effect. An effect is the product of the interaction between a mechanism triggered by the intervention and the context in which the intervention is implemented. A mechanism must be understood as the way in which the actors involved in an intervention reason and react with regard to the resources available within the framework of this intervention [41]. It therefore aims to observe, in a particular context (C), the regular appearance - although not systematic - of a result (O), by triggering a mechanism (M). This view of causality is called generative. The objective is to develop Context-Mechanism-Outcome (CMO) configurations, to explain the intervention and its results. In fact, the realist research will start with a description on the intervention theory of the AIRE project and will lead to the production of a mid-range theory. Intervention theory is “the set of beliefs and assumptions that underpin program activities. Programs are inevitably based on a theory [...] of how activities are supposed to bring about the desired changes” [42].. Mid-range theory, proposed by Merton [43], can be defined as “the level of theoretical abstraction that provides an explanation of observed patterns and regularities in the context-mechanism-outcome interactions of a set of interventions “ [44].

The evaluation of the process will be based on a review of the theoretical and conceptual literature in order to formulate theoretical propositions that will guide the collection of empirical data. For example, we will draw on realist assessments and balances of oxygen delivery to children to develop theoretical propositions specific to the AIRE project [24, 27]. We will also build on the work of a realist evaluation of the IeDA approach to the management of childhood illnesses in Burkina Faso [45]. We will then empirically verify the validity of the various frameworks and theories by confronting them with empirical data using an abductive approach (back and forth between empirical data and theory to produce an explanation of a phenomenon). During these stages, we will involve the country and coordination teams through a participatory approach.

We have chosen to investigate more specifically several lines of research that will then allow us to feed the realist evaluation of the project: acceptability, fidelity of implementation and process.

#### Outcomes evaluation

A population-based cross-sectional study of all children under 5 years of age managed will be conducted in the 16 research PHC implementing the integration of PO into IMCI (electronic or paper) to assess: pathways, patterns, costs of care. A prospective longitudinal follow-up of severe cases until Day-14 after the index IMCI-consultation will document their health outcomes.

##### Study population and patient inclusion process at research sites

Screening and inclusion criteria process (Fig. 4)

**Fig. 4 Fig4:**
[figure not shown]
Inclusion process of children and follow-up in the AIRE research sites. Burkina Faso, Guinea, Mali, Niger, June 2021–June 2022

All the neonates (0 to 59 days) and children (2 to 59 months) attending IMCI consultation in the research sites of the AIRE project will be screened by the HCW in place at the PHC. They will be classified as “red case”, “yellow case” or “green case”, according to routine IMCI guidelines based on their age category.

PO will be introduced after IMCI classification for all children based on age and danger signs, except for those aged 2–59 months and classified as non-respiratory “green case”. Children could be then reclassified as severe cases using PO if SpO2 < 90% defining hypoxemia, as shown in Fig. 4 (red arrow).

Eligible children for whom at least one caregiver gives signed informed consent will be enrolled consecutively during the recruitment period, from 2021, 14th June to 2022, 20th June.

All individuals identified as severe cases (respiratory and non-respiratory) under IMCI guidelines only or using PO should be referred to the hospital: these children will be included in a short-term follow-up study until Day-14 after the index IMCI consultation, regardless of their subsequent hospitalization or not, to document their health outcomes. Data on referral to hospital, and hospitalization of the child, if applicable, will be collected. In the event of hospitalization, care for children with serious respiratory or non-respiratory diseases (oxygen therapy and antibiotic therapy, etc.) will be provided under local conditions with the support of the AIRE project. At Day-14, study team will call or visit the caregivers at home to collect data on the child health status and care pathway through Day-14. Non-severe cases identified at the PHC will return home after the IMCI consultation without further follow-up.

Follow-up supervision, training and data quality control will be provided by the clinical supervisor at operational sites, and clinical research monitors and research assistants at research sites.

### Data collection, management and procedures

#### Context evaluation

A baseline descriptive study using a quantitative e-questionnaire for all PHC and another e-questionnaire for district hospitals has been conducted. The objective of these questionnaires was to describe (non-exhaustive list): distance among PHC and the hospital district, electrical power, its functioning and its capacities in terms of health personnel, supply and delivery services, the type of IMCI used, the PO use, usage of specific public health policies (access to care and prices), capacities and methods of hospital transfer.

Then, all the sites will collect monthly routine aggregated health indicators over the inclusion study period, with a description of the infrastructures, personnel changes and all the characteristics: number of IMCI consultations, number of IMCI consultations using PO, number of respiratory and non-respiratory severe cases, and number of hospitalizations decided by the HCW and accepted by families, stratified by age groups and sex. In all AIRE project sites (operational sites and research sites), this aggregated health data will be extracted from routine activities collected under the responsibility of Ministry of Health staff either at the PHC level or at the health district level.

The Inserm team will develop an operational monitoring tool for sites with REDCap® to be used in each participating site by the country Monitoring & Evaluation officers and district teams to monitor monthly trends.

#### Process evaluation

##### Acceptability

We will first seek to measure and understand the acceptability (quantitatively at all sites and qualitatively in research sites) of the routine use of PO integrated into IMCI by health workers and people who accompany children to PHC. Indeed, the process of acceptability or non-acceptability of an innovation is crucial for understanding the adoption and dissemination (or not) of an innovation. For this study, we will use a conceptual framework built from a scoping review [46] and with the framework’s best-fit synthesis method [47]. We will study acceptability in quantitative terms (via questionnaire based on a Likert scale in all sites), and in qualitative terms (via in-depth interviews, only in research sites). We will analyze acceptability at three time-points: prospective (before PO introduction), concurrent (approximately 6 months after PO introduction), and retrospective (approximately 18 months after PO introduction, and 2 months after the end of the data collection related to child monitoring).

All HCW working in the AIRE sites will therefore be interviewed as part of these sequential surveys. Concerning the child’s accompanying person, a stratified sampling (the strata being linked to variables such as the distance between the place of residence and the PHC, the child’s stage of severity, etc.) will be carried out.

##### Implementation fidelity

Our study of the fidelity of the implementation of the AIRE PO intervention will be carried out in the 16 research sites. It will be based on the analysis framework of fidelity and adaptation to the implementation of Carroll et al. [48] and Perez et al. [49]. We will first list the activities considered essential to the project, based on the official documentation of the AIRE project (implementation guide, action plans, meeting minutes) and interviews with the teams. For each activity listed, we will specify the content (activity implemented), the coverage (population reached by the activity) and the temporality (timing and duration of implementation) in order to assess whether the “active components” of the intervention were received by the “beneficiaries” as often and as long as they should have been. Empirical data will be collected with an implementation fidelity grid and for each activity, respondents will be asked to provide a detailed and documented assessment of its implementation at three levels over the study period: implemented as planned, not implemented as planned or modified, and not implemented. They may also mention other activities that have been added.

##### Process and realist evaluation

The process evaluation will focus on the challenges of introducing and disseminating PO according to the work of Greenhalgh et al. [50–53]. The seven conceptual dimensions presented in their framework will serve as a guide to better understand these challenges, including their influence on the adoption (or not), abandonment, diffusion, scale-up and sustainability of using PO during IMCI consultations.

The realist evaluation will be undertaken based on this same data collection, but will be conducted in accordance with the intervention theory and design approach presented above. For this dual analysis, qualitative empirical data will be collected in the 16 research sites. Data will be collected through interviews and field observations at the 16 research sites to understand how the PO intervention is actually implemented and used in these PHC.

#### Outcomes evaluation

##### Individual data collection

Once enrolled in the AIRE research study, the following data will be collected for each child by the data collector from Day-0 at the PHC level (Table 2): baseline socio-demographic and clinical history data, specific IMCI signs and symptoms and care provided according to the age-specific IMCI classification of national guidelines and WHO guidelines [29, 30, 34, 35]. Non-severe cases identified at the PHC will return home after the IMCI consultation. Then, all severe cases (respiratory and non-respiratory) will be followed up until Day-14 after the index IMCI consultation to document: hospital transfer modalities; pathways of care; models of care at PHC and hospital level; and short-term health outcomes in terms of vital status at Day-14 (Table 2). In all research sites, quantitative and qualitative data will be collected through electronic Case Report From (e-CRF) by specific research data collectors based at PHC level, and a counsellor to ensure the Day-14 vital status follow-up either by phone, or home visit if needed. Each health district has at least one referral health center or district hospital (DH) for the referral of severe cases to be treated according to the adapted WHO guidelines per country [4, 54]. Data will be collected on all patients referred from the PHC research sites to the DH by a research data collector based at each DH.

**Table 2 Tab2:** Collection of individual data according to the children schedule at the AIRE research sites

	Inclusion All IMCI eligible consultation at PHC level	If hospitalized, recommended for all severe cases (respiratory and non-respiratory cases)		Follow-up visit: at the PHC, telephone call or home visit All severe cases regardless of hospitalization
	D-0	Entry	Discharge	Day-14 (+ 14 days)
Inclusion criteria Informed consent	✓			
Socio-demographic characteristics, care pathway before attending PHC, IMCI classification	✓			
Medical history and treatment	✓			
Clinical examination (symptoms and signs) ^a^	✓	✓	✓	
Co-morbidities (malnutrition, anemia, malaria)	✓	✓		
SpO2 Measurement by PO and integration into the IMCI classification (severe case if SpO2 < 90%)	✓	✓	✓	
Use of Malaria Rapid Diagnostic Test (RDT)	✓	✓		
Medical treatment (antibiotics, artemisinin -based combination treatment, salbutamol, etc.)	✓	✓	✓	
Hospital referral decision for severe cases	✓			
Missed opportunities of referral for severe cases and reasons				✓
Oxygen therapy		✓	✓	
Laboratory evaluation, (full blood count, malaria RDT…) if applicable		✓		
Evaluation of response to treatment		✓	✓	
Treatment and management of comorbidities		✓	✓	
Costs (households, and government perspective) ^b^	✓	✓	✓	✓
Vital status			✓	✓

^a^ content of the clinical assessment changes depending on the place of examination

^b^ representative sub-sample of non-severe and severe cases

In addition, a cost study will be conducted for a sub-sample of severe and non-severe cases in research settings from a societal perspective, but also the cost paid by governments and the costs borne by households. Direct medical costs (medical consultations, medicines, hospital transfer, hospital stay), direct non-medical costs (transport to health centers and hospitals, accommodation) and indirect costs (loss of income) incurred by households will be collected. Direct medical costs will include those incurred by the health system (infrastructure equipment, examination and care, PO use, staff costs). From a societal perspective, cost will include the intervention costs (cost of setting up PO in health centers, staff training, equipment, maintenance of equipment, community intervention), direct medical and non-medical costs as well as indirect costs [55]. The cost of soliciting caregivers and the consequent loss of income will be collected through interviews. Expenditure incurred by households will be estimated declaratively using a standardized questionnaire. Activity mapping and resource use will be assessed through semi-structured interviews and guided focus groups. Qualitative information will be collected until saturation is reached. All costs will be expressed in 2021 international dollars. Quantitative cost data will be collected by data collectors under the supervision of health economists. Health economists will estimate the additional project cost intervention through deliberate sampling.

All data collected will be anonymized and stored in the REDCap® database.

##### End of search

All enrolled children, classified as severe cases will be followed up to 14 days after inclusion. The official end of the research, except in the case of premature termination, is defined as the last day of follow-up Day-14 of the last child included in the study.

##### Withdrawal from the study

An investigator may remove a subject from some or all study components at any time at their discretion. In such a case, the investigator will inform the parent(s)/guardian(s) that the child has been withdrawn from participation in the study, and the reasons therefore. In any case, the clinical management of the child will be prioritized over research.

The parent(s)/guardian(s) can decide at any time to withdraw the child from the study if they wish, without justification nor any consequence on the quality of follow-up and subsequent care. In this case, no new information should be collected and recorded in the database after the date of withdrawal. They could also expressly request to delete all previously collected data.

##### Loss to follow-up

A child not withdrawn by consent, deceased or transferred, and whose family does not show up or respond for the follow-up on Day-14 (+ 14 days) will be considered as definitely lost to follow. The follow-up date will be the date of their last contact with the study team (either at the hospital, by phone or at home).

### Sample size

#### Context evaluation

All AIRE PHC in two health districts per country, ie 202 PHC and 8 district hospitals, and their staff concerned were evaluated at baseline and will then be evaluated monthly until the end of the project.

#### Process evaluation

Quantitative acceptability (prospective, concurrent and retrospective): all HCW in charge of using PO in the 202 PHC.Qualitative acceptability in the 16 research PHC (concurrent and retrospective): approximately 64 HCW (approximately 4 per research site) and approximately 64 caregivers (stratified sample to respect the diversity of their situation: age, sex, distance/familiarity with the PHC, health status of the child…).Fidelity of implementation: all HCW in the 16 research PHC, people working with the PHC (managers of drug depots, management committee managers, etc.) and people working at the health district levelProcess and realist evaluation: approximately 20 people per district (HCW, caregivers, members of the management committee, community health workers, etc.).

The principle of empirical saturation (learning nothing new about the subject), usually used in qualitative study will be applied.

#### Outcomes evaluation

Cross-sectional study of pathways and patterns of care will be conducted among all IMCI children eligible for PO use with caregiver consent by research PHC. Children will be recruited consecutively during the 12-month.

Direct and indirect costs will be collected for a representative sub-sample of two categories of children: IMCI outpatients (green and yellow cases) and severe cases requiring hospital transfer (5 per category per PHC per month, i.e. 1920 children in total).

Day-14 health outcome will be collected only for severe cases. To assess the child mortality on Day-14 of all severe cases identified with an accuracy of plus or minus 3% per country and adding 10% lost to follow-up, we aimed to recruit at least 710 severe cases aged 2 to 23 months (mortality estimated at 10%) and 375 children aged between 24 and 59 months (mortality estimated at 5%), i.e. 1085 children between 2 and 59 months old per country over 12 months, for a total of 4340 children. We will only describe mortality in neonates (aged less than 59 days) enrolling them all over the 12 months of the operational study with a maximum of 400 per country. Overall, we will follow a maximum of 1485 children per country, i.e. a maximum of 5940 severe cases over the study period, representing approximately 15% of the total IMCI population which will be a total of 40,000 children expected for the four countries.

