## Methods of the AIRE research protocol

### The AIRE study sites

The AIRE operational research study will be conducted in four AIRE countries where there is a high severe disease incidence: Burkina Faso, Guinea, Mali, Niger. The project will take place in two health districts per country, in a total of 8 district hospitals and 202 PHC (Fig. 3). All PHC will be considered as operational sites (from which aggregate health data will be collected) and 16 research sites will be selected among them (4 sites per country providing also individual health data). Data on the quantitative acceptability of HCW will be collected in both operational and research sites.

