**Fig. 3 Fig3:**
[figure not shown]
Map of intervention sites in the four countries participating in the AIRE project. Burkina Faso, Guinea, Mali, Niger, March 2021–December 2022. Source: [name] who gave her written permission to use it

All project PHC have been selected if they were offering IMCI consultations to children under five and with the agreement of the national authorities. Among these, the research sites were selected according to the following criteria: i) public PHC, ii) PHC fully equipped with the equipment required for the implementation of IMCI consultations, iii) PHC in an area with Internet network coverage available for electronic data collection, iv) PHC accessible to the research team in terms of safety, geographically and for other reasons, regardless of the population accessibility, v) PHC without prior introduction of PO, vi) PHC with no other ongoing research project, vi) PHC with minimal hospital referral management capacity. To ensure size representativeness compared to other PHC at each health district level, a large PHC and a medium/low frequency PHC were selected as research sites. Thus, 16 research sites were selected by the AIRE research team based on the above criteria based on the AIRE site assessment. All research sites were also approved by the national authorities. In Guinea, the AIRE project also implemented specific COVID-19 activities through 29 PHC, including a PO implementation component, but introduced at the triage stage and using a SpO2 threshold of 94% for hospital referral, which differs from the WHO IMCI guidelines. Consequently, these latter sites were not included in the AIRE research sites. A description of AIRE intervention sites per country is summarized in Table 1.

**Table 1 Tab1:** Description of AIRE intervention sites, primary health care centers (PHC) and district hospitals according to countries; March 2021–December 2022

Country	Burkina Faso		Guinea		Mali		Niger		Total
Health districts	Dedougou	Boromo	Matoto	Telimele	Dioila	Markala	Niamey IV	Dosso	
# of operational PHC	49	38	16	15	25	19	10	30	202
# of research PHC	2	2	0	4	2	2	2	2	16
# of district hospital	1	1	1	1	1	1	1	1	8
Type of IMCI support	electronic		paper		paper	electronic	paper		–
NGO implementer	Terre des hommes		ALIMA		ALIMA	Terre des hommes	Solthis		–

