#### Outcome evaluation

##### Descriptive analysis

The analysis will first describe and analyze each of the following results stratified by country:Characteristics of children under 5, eligible for PO during IMCI consultation: distribution by age, sex, distance from home to PHC, socio-demographic variables, rural/urban PHC, clinic IMCI classification, type of case (respiratory or not), PO uptake (%), SpO2 level measurement (mean and % of hypoxemia [severe< 90% and moderate 90 to 93%]) and IMCI+PO classification, IMCI management (on paper/electronic), severe cases (respiratory and non-respiratory) and rate among severe cases with hospital transfer indicated.Pathways of care (in %) stratified according to severity (IMCI+PO) and hypoxemia: history of recent attendance at PHC, duration since the onset of symptoms, effective rate of hospitalization among severe cases (proportion of hospitalizations carried out among all those identified at PHC with a hospital transfer indication, missed referral opportunities among severe cases with indication for hospital referral and reasons for non-transfer, return to PHC care, or rehospitalizations.Patterns of care for IMCI outpatients stratified according to severity (IMCI+PO) and hypoxemia, and for inpatients, hospitalization patterns: coverage of oxygen therapy, antibiotics, ACTs, and other specific treatments in %, volumes, mean time between the medical treatment and onset of symptoms, and the diagnosis of hypoxemia and mean durations of resources utilization.Costs expressed as medians with interquartile ranges, according to the severity of the case, hypoxemia, and the hospitalization by countryShort-term health outcome (deceased, alive and still treated, alive and cured, lost to follow-up) on Day-14 (in %) for all severe cases identified at the PHC level.

Descriptive statistics will include proportions for categories (with their 95% confidence intervals) and means (standard deviation) or medians (interquartile range [IQR]) for continuous variables. Differences in proportions will be tested by the Chi-square test (or Fisher’s exact test in the case of small sample sizes), and continuous variables will be compared using the t-test or Wilcoxon rank-sum test, as applicable.

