##### Cost analysis will describe and analyze

The median overall direct cost of care per child managed (outpatients visits, hospitalization days, drugs, and oxygen, others, …) will be estimated (in USD) in each country according to the different categories of patients (non-severe cases, severe cases not transferred, and severe cases hospitalized). Within each category, we will investigate the effect of the support of IMCI used (paper or electronic) and PO use leading to IMCI reclassification. Indirect costs will be similarly estimated for the severe and non-severe cases.We will compare costs for managing non-severe cases, severe cases not transferred, and severe cases hospitalized using a mixed linear regression model.The PO implementation cost will be assessed exploring the additional cost of PO use for the health system and the remaining costs for households according to the severity of cases, the pathway of care and the patterns of care and will be studied in the 4 countries of the project.

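### Costs are specified in two different currency units, and the cost sub-sample called representative is an equal quota per health centre and month that mirrors the caseload only if weighted

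*Protocol article*

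**What the plan says.** **Currency.** The protocol article, under Individual data collection, states: "All costs will be expressed in 2021 international dollars". The section on the cost analysis states that the median overall direct cost per child "will be estimated (in USD) in each country according to the different categories of patients". It gives no price year.

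**Sampling.** The Sample size section (Outcomes evaluation) says: "Direct and indirect costs will be collected for a representative sub-sample of two categories of children". The categories are "IMCI outpatients (green and yellow cases) and severe cases requiring hospital transfer", and the size is "5 per category per PHC per month, i.e. 1920 children in total". Footnote b of Table 2 repeats the claim of representativeness. The section on study sites says that "16 research sites will be selected among them (4 sites per country providing also individual health data" and that, in each district, "a large PHC and a medium/low frequency PHC were selected as research sites".

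**Summary measure.** Under Descriptive analysis: "Costs expressed as medians with interquartile ranges, according to the severity of the case", and also by hypoxemia and hospitalization, by country. The cost analysis section gives country medians for three groups: non-severe, severe but not transferred, and severe hospitalized. The article does not say whether these medians are weighted, or how the five children are picked within a PHC and month.

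**The concern.** There are two separate problems.

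First, the unit. An international dollar is a purchasing-power unit, and a US dollar is a market currency. The first rule covers all costs, so the second is not an exception to it. Both govern the same result, the direct cost per child in each country. The gap between the two units differs from country to country, so the choice can alter how the four countries compare.

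Second, the label. Equal numbers from large and small PHCs, and from peak and slack months, mean that the chance of being sampled falls as caseload rises. The article itself gives reasons why cost could vary along those lines. Household costs include transport, collection spans 12 months because of seasonal disease, and the Discussion describes different care-seeking in urban and rural populations. If the sample is taken at its label and analysed without weights, a figure presented as a country's cost per child describes a different mix of children from the one enrolled.

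**Working it through.** **Step 1. The plan's own total.** Inputs: 5 children, 2 categories, 16 research PHCs, 12 months.

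5 × 2 × 16 × 12 = 1920, which reproduces the stated figure. It gives 1920 / 2 = 960 per category, 960 / 4 = 240 per category per country, and 5 × 12 = 60 per category per PHC, whatever the PHC's volume.

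**Step 2. Sampling fractions by severity.** Inputs from the Sample size section: at most 5940 severe cases among 40,000 children expected. I take 40,000 as the common denominator.

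- Severe: 960 / 5940 = 16.2%.
- Non-severe: 960 / (40,000 − 5940) = 960 / 34,060 = 2.8%.
- Ratio: 5.7.
- With 4340 severe cases (the target without neonates): 960 / 4340 = 22.1% against 960 / 35,660 = 2.7%, ratio 8.2.

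**Step 3. Shift of an unweighted median within one severity stratum.** The documents give no PHC volumes or costs, so these are assumptions. Take one large and one small PHC with volume ratio V, log-normal costs with log-SD s of 0.8 or 1.0, and cost ratio R between the PHCs. The median m solves

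w·Φ((ln m − ln a)/s) + (1 − w)·Φ((ln m − ln b)/s) = 0.5,

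where a and b are the median costs in the large and small PHC. The quota implies w = 1/2. The caseload implies w = V/(V + 1). The shift is the quota median divided by the caseload median, minus 1.

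| V | R | Small PHC costlier | Large PHC costlier |
|---|---|---|---|
| 1 | any | 0% | 0% |
| any | 1 | 0% | 0% |
| 2 | 1.25 | +3.8% | −3.7% |
| 3 | 1.5 | +10.8% | −9.7% to −9.8% |
| 5 | 2 | +26.6% to +27.0% | −21.0% to −21.2% |

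The same arithmetic applies to peak and slack months in place of large and small PHCs.

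**Step 4. Where severities are mixed.** The sample is 50:50 severe to non-severe. The expected caseload is 5940 / 40,000 = 14.85% severe. With log-SD 1.0 and full pooling, the unweighted median divided by the weighted one is 1.28 if severe cases cost twice as much (assumed), 1.86 at five times and 2.56 at ten times. Full pooling is the upper case. A table by hypoxemia or hospitalization alone would mix severities only in part, for example among non-hospitalized children.

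**Step 5. Currency.** One section puts all costs in 2021 international dollars. The other puts the median direct cost in USD with no year. The documents give no conversion factors, so the size of the discrepancy cannot be computed from them.

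**The case against.** The strongest reply is that this is a condensed article with no SAP shown. Weights, and the rule for choosing five children in a PHC-month, are details that normally sit in the fuller documents, and no text says that the medians are unweighted. That stands. It limits the point to what can happen if weights are not used. A reader might infer that the sample is simply not representative, or that the medians will be wrong. Neither follows: an equal allocation over strata can represent the caseload when selection within strata is sound and the estimates are weighted. What remains is that the article attaches the word to a flat quota and specifies the cost analysis without the condition that would justify it.

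The medians in the cost analysis section are also separated by severity, so the 5.7-fold oversampling of severe cases does not by itself bias them. That stands too. It matters only in tables that mix severities.

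Other tempting extensions are not supported:

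- **Direction.** One might infer that country costs are overstated because small PHCs count too much. The sign depends on whether small or large PHCs cost more, and nothing in the article settles that.
- **Model.** One might read the mixed linear regression as fitted to raw skewed costs. The article names no scale, and a log-transformed outcome fits its wording.
- **Medians as such.** One might object that medians cannot be summed into a budget for scale-up. The article treats the cost of implementing pulse oximetry as a separate analysis and does not say that child-level medians will feed it. Median with interquartile range is a conventional description of skewed costs.

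On currency, one could say that USD was meant loosely for international dollars. That is possible, but the two rules as written differ and should be reconciled.

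**Conclusion.** The currency conflict is certain on the text: two incompatible units for the same country-level result, one with a price year and one without.

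The sampling point holds conditionally. The quota is not self-weighting across PHCs or months, so it reflects the enrolled caseload only with weights, or if cost is unrelated to PHC volume and season. An unweighted country median within a severity stratum can be off by 0% to about 27% in size, sign unknown, over assumed volume ratios of 1 to 5, cost ratios of 1 to 2 and log-SDs of 0.8 to 1.0. The documents do not locate the study within that range. Mixing severities can add a larger error, up to the 1.3- to 2.6-fold of the fully pooled case at assumed cost ratios of 2 to 10. The sample size of 1920 is not in question.

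**What to change.** 1. **Unit.** State one currency unit and one price year under Individual data collection and in the cost analysis section. If the other unit is wanted, report it as a conversion with the factors used.
2. **Label.** In the Sample size section and the Table 2 footnote, replace the claim of representativeness with a description: an equal-quota sample stratified by PHC, month and severity category. Add the rule for selecting the five children, or a pointer to where it is given.
3. **Weights.** State that country cost summaries, including the medians already planned, weight each sampled child by (children enrolled in that PHC, month and category) / (children sampled there). Consecutive enrolment supplies the counts. The weights restore the enrolled caseload, that is, consenting children eligible for pulse oximetry, and not all attenders.

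The cost is wording and analysis code, with no new data. Weighting widens intervals slightly. For two equally sampled PHCs with volume ratio V, the usual approximation to the variance inflation is 2(V² + 1)/(V + 1)². This is 10/9 = 1.11 at V = 2 and 20/16 = 1.25 at V = 3, so intervals are about 5% and 12% wider. At the extreme of V = 5 it is 52/36 = 1.44, about 20% wider.
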